## 2.4 Secondary Outcomes

1. Rates of hyperbilirubinemia requiring phototherapy or hospitalization
2. Poor infant weight gain requiring intervention (pumping, supplementation, hospitalization)
3. Incidence of breastfeeding difficulties (e.g., sore nipples, insufficient milk supply, inadequate latch, engorgement)
4. Breastfeeding self efficacy score (Breastfeeding Self Efficacy Scale or BSES) at 2 weeks, 1 month and 3 months
5. Score of the Edinburgh Post-partum Depression Scale for new mothers
6. Access to community-based services: Public Health Clinics, Family Doctor, Pediatrician
7. Number of emergency department visits for the mother and the baby
8. Number of hospital readmissions for the mother and her baby
9. Mothers' satisfaction with the support received
10. Length of stay in the hospital, from delivery to discharge
11. Costs associated with this community-based postpartum clinic.

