### 3.2 Events prior to hospital discharge

#### 3.2.1 Data collection

Once consent has been obtained, the research team will collect information about delivery (mode of delivery and date and time of birth), obstetrical (previous pregnancies, parity) history, and information on the baby (gender, ethnicity, gestational age at birth, birth weight, Apgar score, bilirubin levels (TCB [trans cutaneous bilirubin] and/or TSB [total serum bilirubin], whether supplementation was given and date and time of discharge) from the hospital chart.

Contact information will be recorded in the study master log. As well, the OHIP number will be recorded in the master log to eventually allow the linkage of the dataset to ICES administrative data.

Upon confirmation by the pediatrician, the obstetrician, the family physician, and/or the midwife in attendance that the mother and baby have no counter-indication for early discharge, the research team will proceed to randomize the participant.

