### **3.4 Intervention arm post-discharge events**

Women randomly assigned to the intervention will be discharged approximately 24 hours following a vaginal delivery or approximately 48 hours following a C-section. While this is the aimed ideal time of discharge, there may be variation as time of discharge will ultimately depend on the attending physician/midwife's opinion/orders and what he/she feels is in the best interest of the mother and her newborn. Women who choose to stay in the hospital longer will still be referred to the Monarch Clinic and will not be excluded from the study.

Women and their infants will be expected to attend a pre-booked appointment at the breastfeeding clinic, scheduled within 48 hours of their discharge. Clinic staff will follow up with the participant if she fails to keep the mandatory follow-up appointment. This first appointment will include maternal assessment and care (e.g., wound care, prescriptions), neonatal care (e.g., tongue-tie clips, jaundice screening using transcutaneous bilirubinometer), blood work including TSB (samples couriered to TOH central laboratory, HBHC postpartum assessment, and breastfeeding assessment and support. Family physicians will be available for on-site consultations in the mornings, and lactation consultants and registered nurses will be at the clinic throughout the day from Monday to Friday and Saturday mornings. Medical data (e.g., bilirubin level (transcutaneous and serum), newborn assessment, infant weight gain, urination and defecation frequency, breastfeeding assessment and progress, maternal care) found in the clinic chart will be gathered.

The Bilirubin Pathway, established by the CMNRP, will be used to guide for the management of neonatal jaundice. Those guidelines provide recommendation for subsequent TSB and or TCB follow-up, according to the modified Buthani's normogram and whether risk factors for hyperbilirubinemia are

present or not. For babies discharged before 24 hours, blood for the newborn screening will be drawn at the first visit and sent by mail to the Newborn Screening Ontario laboratory located at CHEO.

Additional follow-up visits at the breastfeeding clinic will be made available to participants for the month following the birth of their baby.

Participants in the intervention group will also be contacted at 2 weeks, 1 month and 3 months to complete the different surveys and questionnaires (3.5).

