| Maternal care and neonatal care (jaundice screening using transcutaneous bilirubinometer and weight gain assessment) at the clinic. |   | X |   |     |     |     |     |     |
| Breastfeeding support at clinic                                                                                                     |   | X | X |     |     |     |     |     |
| Additional medical care at clinic                                                                                                   |   |   | X |     |     |     |     |     |
| Collection of medical data from visits at clinic                                                                                    |   | X | X |     |     |     |     |     |
| Demographics survey                                                                                                                 |   |   |   |     |     | X S |     |     |
| Edinburgh Postnatal Depression Scale                                                                                                |   |   |   |     | X S | X S |     |     |
| Breastfeeding local complications survey                                                                                            |   |   |   | X S |     | X S |     |     |
| Breastfeeding survey                                                                                                                |   |   |   | X S |     | X S | X S |     |
| Use of resources survey                                                                                                             |   |   |   | X S |     | X S | X S |     |
| Self-efficacy survey                                                                                                                |   |   |   | X S |     | X S | X S |     |
| Mother Satisfaction Survey                                                                                                          |   |   |   |     |     |     | X S |     |
| 6 month follow up survey                                                                                                            |   |   |   |     |     |     |     | X S |

Index: X = Women assigned to the breastfeeding clinic program will be completing these events

S = Women assigned to the standard care will be completing these events

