### 4.3 Statistical analysis

All outcomes will be analyzed based on the intention-to-treat principle, in accordance with the randomization allocations described previously. The primary goal of this study is to test the hypothesis that rates of exclusive breastfeeding at 3 months (defined as the feeding of only the infant's mother's milk for at least 2 weeks prior to collected outcome) will be higher in the group of women attending the post-partum clinic, as compared to those under standard of care. For comparison between intervention and control arms we will employ a generalized estimating equation multivariable regression model to account for prognostic risk factors that have not been sufficiently balanced by randomization. Group and individual level covariates will be included in the model, with recruitment site as the clustering unit to allow for inference at the individual level. This design will also investigate the effect of demographic

drivers such as maternal age, education, parity, etc., on the primary outcome, producing both crude and adjusted risk estimates and their 95% confidence intervals.

Secondary outcomes will be collected by studying the medical data (such as rates of hyperbilirubinemia and self-efficacy) that will be entered in the database by the research staff. This data will be compared across case and control groups using the Pearson Chi-squared, Student's t, or Fisher's exact test, depending on their observed frequencies. We will also compare the statistics and outcomes from the present study with baseline estimates from phase 1. The answers women provide through their questionnaires and surveys will be the main instruments for determining exclusive breastfeeding rates and their behavioral and emotional measurements. For the cost-effectiveness analysis, direct and indirect costs for the intervention and control groups will be compared regarding use of resources (e.g., clinic visits, physician visits, Emergency Department visits, hospital readmission, and indirect cost).

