## **5 Data management**

### **5.1 Data collection**

Data collected from participant charts and during phone interview will be recorded by research personnel in a web-based Case Report Form created using the secure platform: REDCap. Each participant will be identified by a unique ID number.

Details regarding delivery, obstetrical history, and information on the baby will be abstracted from the charts.

Information from the clinic visits including referrals will be abstracted from the clinic charts.

Data will also be collected by the means of surveys sent to the mother. Participants completing surveys online will receive a link by E-mail to complete the surveys. Upon clicking on the "submit" button the survey will be sent to research database and will no longer be available to the participant.

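### Two secondary outcomes are tested between arms, but the only post-discharge medical record named for abstraction is the clinic chart, which only the intervention arm has

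*Protocol*

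**What the plan says.** Section 2.4 of the Protocol lists as its first two secondary outcomes "Rates of hyperbilirubinemia requiring phototherapy or hospitalization" and "Poor infant weight gain requiring intervention (pumping, supplementation, hospitalization"). Section 4.3 gives the source: "Secondary outcomes will be collected by studying the medical data (such as rates of hyperbilirubinemia and self-efficacy"). It continues: "This data will be compared across case and control groups using the Pearson Chi-squared, Student's t, or Fisher's exact test". The same section makes the questionnaires the main instrument for breastfeeding rates and for behavioural and emotional measures; it does not assign jaundice or weight gain to them.

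For the intervention arm after discharge, section 3.4 describes a pre-booked first visit that includes jaundice screening, and says what is gathered from the clinic chart: "Medical data (e.g., bilirubin level (transcutaneous and serum), newborn assessment, infant weight gain" and other items. Section 5.1 adds: "Information from the clinic visits including referrals will be abstracted from the clinic charts". In the section 3.8 calendar, the row "Collection of medical data from visits at clinic" is marked for the clinic arm only. So is the row for jaundice screening and weight-gain assessment.

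For the control arm, section 3.3 provides usual community care and no access to the clinic. Both arms share the hospital chart before discharge (section 3.2.1), the surveys (section 3.5) and the investigators' review of readmissions within 15 days of discharge (section 6.1). Section 3.2.1 also says that "the OHIP number will be recorded in the master log to eventually allow the linkage of the dataset to ICES administrative data".

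**The concern.** If section 4.3 is followed as written, one arm has scheduled screening and an abstracted chart after discharge, and the other has no medical record assigned in its place. Weight gain is largely a post-discharge matter here, because the intended discharge is at about 24 hours after vaginal birth or 48 hours after Caesarean section. Pumping and supplementation are also steps that a lactation clinic is likely to advise and to write down.

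Fuller recording in one arm yields more recorded events there even when the true rates are equal. The clinic could then appear to increase jaundice treatment or weight problems, or a real reduction could be hidden. Preventing costly postnatal problems is part of Objective 1, and section 1 names jaundice as one of the problems meant. A later analysis plan can choose among the data collected, but it cannot supply control-arm events that were never asked about or abstracted.

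**Working it through.** The plan states no figure on this point, so there is none to reproduce. The check is to trace each source by arm and then illustrate the size on assumptions.

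**Step 1: sources by arm**

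| Source | Intervention | Control | What it shows |
|---|---|---|---|
| Hospital chart to discharge (3.2.1) | yes | yes | bilirubin, birth weight, supplementation |
| Clinic chart (3.4, 5.1) | yes | no (3.3) | bilirubin, weight gain, care given |
| Surveys (3.5) | yes | yes | feeding, complications, resource use, infant readmission; forms not shown |
| Readmission review to 15 days (6.1) | yes | yes | hospitalization |
| ICES linkage (3.2.1) | possible | possible | tied to no outcome in the protocol |

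**Step 2: outcome components after discharge**

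- Hospitalization, in either outcome: visible in both arms.
- Phototherapy without readmission: no common source is named.
- Pumping or supplementation for poor weight gain: no common source is named. The feeding survey may pick up supplementation, but section 3.5 does not say that it records the reason.

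**Step 3: illustration of size**

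Inputs:
- Arm sizes of 306 and 154, from section 4.1. These are recruitment targets before losses.
- Assumed, because the documents give neither: the same true event rate p in both arms; capture of 95% in the intervention arm; capture of 80% or 60% in controls.

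Formula: recorded rate = p × capture. With equal true rates, p cancels, so the apparent risk ratio = 0.95 / control capture.

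- Control capture 80%: 0.95 / 0.80 = 1.19.
- Control capture 60%: 0.95 / 0.60 = 1.58.

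Chance of a false finding against the clinic, using a two-sided 5% test with the normal approximation: Φ[(d − 1.96·SE0)/SE1]. Here d is the difference in recorded rates, SE0 the pooled and SE1 the unpooled standard error.

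Worked case, p = 10% and control capture 80%: recorded rates are 9.5% and 8.0%, so d = 0.015. SE0 = 0.0283 and SE1 = 0.0275. (0.015 − 1.96 × 0.0283)/0.0275 ≈ −1.47, and Φ(−1.47) ≈ 7%.

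| True rate | Control capture 80% | Control capture 60% |
|---|---|---|
| 5% | 4.75% vs 4.0%: 5% | 4.75% vs 3.0%: 12% |
| 10% | 9.5% vs 8.0%: 7% | 9.5% vs 6.0%: 23% |
| 15% | 14.25% vs 12.0%: 9% | 14.25% vs 9.0%: 35% |

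Each cell gives the recorded rates and then the chance of a significant excess in the clinic arm. With equal capture and equal true rates, that chance would be the nominal 2.5% in this direction (5% over both).

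**The case against.** The strongest reply is that the wording of section 4.3 is too loose to prove a clinic-only source. The same parenthesis calls self-efficacy medical data, although it is a survey score collected in both arms, and poor weight gain is not named there at all. The survey forms in section 8 are not shown and may contain the needed items. They were used in the pilot, which had the aim of estimating baseline outcome rates; that suggests they capture some outcomes without a clinic chart. This stands as a limit: absence of the items cannot be asserted. It does not remove the point, because no section assigns the surveys, or any other shared source, to these two outcomes.

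A second reply is that screening and weight checks are part of the intervention, so extra treatment that follows from them is a real effect of the clinic. That is right for treatment actually given. It does not cover the same treatment, given in both arms, being recorded in only one.

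A third is that naming a source for each outcome belongs in the analysis plan or case report form. This would hold if data from a common source were certain to be collected; the protocol does not ensure that.

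A reader might infer something stronger: that all jaundice and weight-gain data after discharge exist only for the clinic arm, or that every clinic baby is screened. The documents do not support either. Readmission is seen in both arms, the jaundice outcome is defined by treatment and not by a screened value, and section 3.4 allows for missed first visits.

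**Conclusion.** The concern holds in limited form. As written, the protocol plans direct between-arm tests of two secondary outcomes, while the only post-discharge medical record it names for abstraction exists in one arm. The exposure is mainly in pumping and supplementation for weight, and in phototherapy without readmission. It disappears for any component that the unseen survey forms already cover in both arms. Hospitalization is covered in both arms, and the primary outcome, which is survey-based, is untouched.

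The size cannot be derived from the documents. On the assumed capture rates, the apparent risk ratio is about 1.2 to 1.6 with equal true rates. At the mild end (80% control capture) the chance of a false significant excess is 5% to 9%; at 60% it is 12% to 35%. The expected direction is against the clinic, which could suggest harm or hide benefit. The change should be made before follow-up, because missing control-arm data cannot be recovered by analysis.

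**What to change.** In section 4.3, state that between-arm comparisons of these two outcomes use only sources applied identically to both arms:

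- the same maternal survey items at 2 weeks and 1 month on phototherapy, on pumping or supplementation for weight, and on hospitalization, added if the forms do not already have them;
- hospital or ICES records, through the OHIP number already collected.

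Use clinic-chart bilirubin and weight data only to describe the intervention arm. Apply one definition of pumping and supplementation to both arms. Do not exclude clinic-initiated events: that would remove events from one arm only, while the same advice from a control woman's family doctor or public health nurse would still count.

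The cost is a few survey items and a sentence or two in section 4.3. The downside is that clinic-chart detail is not used comparatively.

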#### 3.2.2 Randomization

Study participants will be randomly assigned to either the intervention (discharge with follow-up at the breastfeeding clinic) or the control (standard of care) groups via a 2:1 allocation ratio, with group designations being determined after the patient is enrolled and informed consent is obtained. Stratification will be used to improve allocation balance by site of recruitment and parity of participants. Group designation is given from a randomization list, which will be generated using a permuted randomized block design, with permuted blocks of sizes 3, 6, and 9 units, prior to study initiation. This list is then entered directly into REDCap's group allocation component which assigns group placement based on the inputted randomization list at the time of initial data entry, all the while blinding the study researchers, recruiters, and participants to the randomization allocations prior to patient enrollment and data collection. The study staff will then inform the participant of their randomization group. Rather than occurring at the time of consent, randomization will be delayed until confirmation by the nurses and/or attending physicians that the participant is indeed a candidate for discharge at approximately 24h ( $\pm$  12) after vaginal or 48h ( $\pm$  12) after C section delivery.

[figure not shown]

**FIGURE 1. Schematic diagram showing the two possible outcomes after randomization.** In the case of this breastfeeding study, the participants may be assigned the standard-care or the post-partum clinic option.

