## 4 Statistics

### 4.1 Sample size

Based on an estimated 50% rate of exclusive breastfeeding at 3 months in the control group, 200 patients per group will be needed to detect a 15% relative difference in the intervention group ( $\alpha=0.05$ ,  $\beta=0.9$ , one-sided test). Assuming an attrition rate of 15% (i.e. loss to follow up, unsuitability, or other unanticipated events), we set a target of **230 participants per group** making a total of **460** women. Accounting for the logistical concern of making full use of the nursing staff, lactation consultants, and family physicians at the clinic, we decided to apply a 1:2 ratio for control to intervention allocations and determined that 154 and 306 patients are needed for the control and intervention groups respectively (maintaining significance level, power, and effect size).

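### Secondary comparisons ignore the stratification by site and parity: the tests are valid, but adjusting for both factors would recover some precision at no cost where they are prognostic

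*Protocol*

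**What the plan says.** On allocation, Protocol 3.2.2 states "Stratification will be used to improve allocation balance by site of recruitment and parity of participants". The list is generated "with permuted blocks of sizes 3, 6, and 9 units" and participants are assigned "via a 2:1 allocation ratio", intervention to control.

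On analysis, Protocol 4.3 treats the two kinds of outcome differently. The paragraph built around the primary hypothesis describes a multivariable generalised estimating equation model with site as the clustering unit. It lists parity among the factors to be examined for the primary outcome and promises crude and adjusted estimates. The next paragraph turns to the secondary outcomes: "This data will be compared across case and control groups using the Pearson Chi-squared", Student's t or Fisher's exact test, with the choice left to the frequencies observed. It names no stratification or covariate. Costs, the last item in 2.4, are compared in a separate sentence without a named test.

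**The concern.** An analysis normally reflects the restrictions placed on the randomisation. Allocation within site-by-parity strata keeps the arms nearly balanced on both factors, so differences between strata largely drop out of the treatment contrast. A plain chi-squared or t test still counts those differences as noise. If the factors predict the outcome, the standard error is overstated, the true type I error falls below nominal, any interval built on that standard error is too wide, and power is given away.

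The secondary outcomes carry much of Objective 1 (2.1) and the secondary hypothesis (2.2). The sample size in 4.1 was set for the primary outcome only, so these comparisons have no planned margin of power.

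**Working it through.** **Plan's own figure.** There is none on this point. The protocol gives no rate, standard deviation, effect size, significance level or power for any secondary outcome, and no measure of how strongly site or parity predicts one. The calculation in 4.1 ("estimated 50% rate of exclusive breastfeeding at 3 months in the control group") concerns the primary outcome, and nothing below depends on it.

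**Inputs from the protocol.** Two recruitment campuses (2.5); stratification by site and parity, blocks of 3, 6 and 9, ratio 2:1 (3.2.2); "154 and 306 patients are needed for the control and intervention groups respectively", a total of 460; attrition of 15% (4.1). Evaluable women: 460 × 0.85 = 391.

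**Assumptions.** Two parity levels, hence four strata (the number of levels is not given); two-sided 5% tests; and R², the share of outcome variance explained by the strata, shown as a range.

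**Step 1: formula.** With arms balanced within strata, the unstratified standard error is too large by the factor 1/√(1 − R²). Rejecting at 1.960 on the unstratified scale is therefore the same as requiring the correctly scaled statistic to exceed c = 1.960/√(1 − R²).

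- True type I error = 2 × [1 − Φ(c)].
- Power, where a stratified test would have 80%: 1 − Φ(c − 2.802), with 2.802 = 1.960 + 0.842.

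Worked case, R² = 0.10: c = 1.960/√0.90 = 2.066; type I error = 2 × [1 − Φ(2.066)] = 3.9%; power = 1 − Φ(2.066 − 2.802) = 1 − Φ(−0.736) = 76.9%.

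| Assumed R² | c | True type I error | Power (stratified test 80%) | Loss, points |
|---|---|---|---|---|
| 0 | 1.960 | 5.0% | 80.0% | 0 |
| 0.01 | 1.970 | 4.9% | 79.7% | 0.3 |
| 0.02 | 1.980 | 4.8% | 79.4% | 0.6 |
| 0.05 | 2.011 | 4.4% | 78.5% | 1.5 |
| 0.10 | 2.066 | 3.9% | 76.9% | 3.1 |
| 0.20 | 2.191 | 2.8% | 72.9% | 7.1 |

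**Step 2: simulation of the design.** The formula assumes exact balance, which incomplete blocks and attrition disturb. The design was therefore simulated for binary outcomes with stratified 2:1 blocks of 3, 6 and 9, 460 randomised, about 391 retained at random, four strata and 6,000 trials per scenario. The assumed true effect was 15 points, or 6 points for the rare outcome. Each cell gives unstratified Pearson chi-squared, then Cochran-Mantel-Haenszel.

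| Assumed stratum differences | Type I error | Power |
|---|---|---|
| None | 4.7% / 4.7% | 81.4% / 81.2% |
| Parity gap 10 points (R² about 0.01) | 4.7% / 4.9% | 81.0% / 81.0% |
| Parity gap 20 points (R² about 0.04) | 5.0% / 5.3% | 82.2% / 82.8% |
| Parity gap 30 points, site gap 5 (R² about 0.09) | 3.8% / 4.8% | 83.0% / 85.7% |
| Rare: 5% against 2% by parity | 4.5% / 4.6% | 60.7% / 60.9% |

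The simulation standard error is about 0.3 points at a 5% level (√(0.05 × 0.95/6,000) = 0.0028) and about 0.5 points for power near 80%. The results agree with the formula within that error. Fisher's exact test rejected in 3.2 to 4.3% of null trials, including 4.1% when the strata had no effect at all.

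**The case against.** The strongest reply is that nothing here is invalid. The named tests hold the type I error at or below nominal, the protocol claims no power for any secondary outcome, and simple tests for secondary outcomes are a defensible, conservative choice. All of that stands, and it limits the point to an improvement.

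A reader might infer that every secondary p-value is too conservative. The documents do not support this. The loss exists only where site or parity predicts the outcome, which the protocol does not quantify, and costs have no named test.

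A reader might also expect a large loss. A parity gap of 40 points with a site gap of 10 would give R² of about 0.17 and a true level near 3.1%, but nothing in the protocol supports gaps of that size. A loss of power for emergency visits and readmissions, the subject of the secondary hypothesis, is not shown either: no rates are given, and if these events are uncommon the effect is close to nil. For length of stay, the discharge targets in 3.4 depend on mode of delivery, which is not a stratification factor.

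Where Fisher's test is used, its own conservatism exceeded the stratification effect in most scenarios, and an exact stratified test would not obviously remove it. That also stands.

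Two replies carry less weight. The model sentence in 4.3 refers to comparison between arms in general, so it could be read as covering secondary outcomes. But it follows directly from the primary hypothesis, the estimates it promises are tied to the primary outcome, and the secondary data then receive tests of their own. A separate analysis plan may add adjusted analyses, but the protocol has not left the matter open: it names the tests.

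**Conclusion.** The mismatch between 3.2.2 and 4.3 is real and is a stated choice of method. Its consequence is some lost precision where site or parity is prognostic. It does not inflate false positives and makes no stated figure wrong. The loss against 80% power is under 1 point for R² up to 0.02, and grows to about 7 points only if the strata explain a fifth of the outcome variance. These sizes rest on assumed R² values, two parity levels, near-balance within strata and two-sided 5% testing. The point is modest in priority, but worth taking because the remedy costs nothing.

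**What to change.** In Protocol 4.3, replace the sentence on secondary-outcome tests so that the comparisons account for site and parity, categorised as in the randomisation:

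- **Binary outcomes:** Cochran-Mantel-Haenszel test with a stratified risk difference over site by parity, in an exact version where data are sparse.
- **Continuous outcomes** (such as the self-efficacy score): linear regression on arm, site and parity.
- **Counts** (emergency visits, readmissions): count regression with the same two factors.

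The cost is a change of wording. Site and parity must be known to randomise within strata, and parity is already abstracted from the chart under 3.2.1, so no new data are needed and the sample size does not change.

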### **3.3 Non-intervention arm post-discharge events**

Women randomly assigned to the non-intervention arm option will be discharged according to the current hospital standards, in accordance with their physician or midwife's decision. After hospital discharge, the participant and her baby will be entitled to receive follow-up care and seek breastfeeding support that is currently available in the community (e.g. through their family doctor, Public Health Unit or private services), but may not attend the pilot breastfeeding clinic.

Women will be contacted at 2 weeks, 1 month and 3 months post-delivery to complete the different surveys and questionnaires (3.5).

As is current standard of care practice, women will be assessed by Public Health Nurses for post-partum depression shortly after birth. Services will be provided as per the standard.

As part of the research, women will be contacted by phone at 3 weeks by a Public Health Nurse to administer the Edinburgh Postnatal Depression Scale. In the event of a high score, the Ottawa Public Health Nurse will provide the participant with appropriate support. Information collected will be abstracted by the research staff.

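### Student's t, the only test listed for secondary outcomes compared as means, does not hold its level under 2:1 allocation if the arms differ in spread; an unequal-variance method would, at almost no cost (minor)

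*Protocol*

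**What the plan says.** Section 4.3 gives one sentence to the comparison of secondary outcomes between arms. They are to be "compared across case and control groups using the Pearson Chi-squared, Student's t, or Fisher's exact test, depending on their observed frequencies". The list is closed: it has two tests for categorical data and one for means. It does not map tests to outcomes, and it does not say which form of the t-test is meant.

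Section 2.4 includes outcomes that are naturally compared as means: the BSES score at three times, the EPDS score, and "Length of stay in the hospital, from delivery to discharge". It also lists counts, such as "Number of emergency department visits for the mother and the baby" and "Number of hospital readmissions for the mother and her baby".

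Participants are randomized "via a 2:1 allocation ratio" (section 3.2.2), and section 4.1 states that "154 and 306 patients are needed for the control and intervention groups respectively".

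On discharge timing, section 3.4 says "Women randomly assigned to the intervention will be discharged approximately 24 hours following a vaginal delivery or approximately 48 hours following a C-section", while under section 3.3 control women "will be discharged according to the current hospital standards".

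**The concern.** Student's t, as the name is ordinarily used, estimates one common variance from both arms. With equal arms, the resulting standard error is right on average even when the two variances differ. With 2:1 arms it is not, because the larger arm dominates the pooled variance while the smaller arm contributes most of the uncertainty in the mean difference. If the smaller arm is the more variable, the standard error is too small and false positives rise. If the larger arm is the more variable, the standard error is too large and power is lost.

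Length of stay is the exposed outcome because the intervention acts on it directly. The larger arm has a discharge target and the smaller arm follows usual practice. That makes greater spread in the smaller arm plausible, which is the anti-conservative direction. Length of stay is also named in Objective 1 (section 2.1), although that objective opens with exclusive breastfeeding, which has its own regression model in section 4.3.

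**Working it through.** **Plan's own figure.** There is none to reproduce. The protocol gives no SD, significance level or power for any secondary-outcome test. The sample-size figures in section 4.1 concern the primary outcome and serve here only as arm sizes.

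**Inputs.** Control n_c = 154 and intervention n_i = 306 (section 4.1). Nominal two-sided level 5% (assumed). Ratio r = control SD / intervention SD (assumed, over a range). Intervention SD set to 1.

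**Formulas.**
- True variance of the mean difference: V = r²/154 + 1/306
- Variance that the pooled test expects: P = [(153 r² + 305)/458] × (1/154 + 1/306)
- Standard-error ratio: k = √(P/V)
- Actual size: 2 × [1 − Φ(1.96 k)]

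**One case in full, r = 1.5.**
- V = 2.25/154 + 1/306 = 0.01461 + 0.00327 = 0.01788
- P = (649.25/458) × 0.009762 = 1.4176 × 0.009762 = 0.01384
- k = √(0.01384/0.01788) = 0.880, so the standard error is 12% too small
- Size = 2 × [1 − Φ(1.724)] = 0.085

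**Range.**

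| Control SD / intervention SD | k | Actual size, nominal 5% two-sided |
|---|---|---|
| 0.5 | 1.223 | 1.7% |
| 0.67 | 1.135 | 2.6% |
| 0.8 | 1.076 | 3.5% |
| 1.0 | 1.000 | 5.0% |
| 1.25 | 0.930 | 6.8% |
| 1.5 | 0.880 | 8.5% |
| 2.0 | 0.818 | 10.9% |

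If the secondary tests were one-sided at 5%, as in the sample-size statement, the sizes at ratios 1.25, 1.5 and 2 would be 6.3%, 7.4% and 8.9%. Reducing the arms to 131 and 260 for the protocol's 15% attrition leaves the two-sided results unchanged to within 0.1 percentage point, because the allocation ratio is the same.

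**Same test at 1:1.** With 230 per arm, V = (r² + 1)/230 and P = [(r² + 1)/2] × (2/230), which is the same quantity. So k = 1 and the size is 5.0% at every r. The sensitivity comes from the allocation.

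**Simulation check** (20,000 trials per setting, 154/306, equal means).
- Normal data, ratios 1.25, 1.5 and 2: pooled test 7.0%, 8.2% and 10.9%; Welch 4.9%, 4.9% and 5.0%.
- Skewed (gamma) data, control/intervention SDs of 0.5/0.33 and 0.6/0.3: pooled 8.6% and 10.8%; Welch 5.1% and 4.9%. With 0.33/0.5: pooled 2.8%, Welch 5.2%.

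**What ratio might length of stay have?** The delivery-mode mix is common to both arms and pulls the SDs together. Assume a 24 h gap in mean stay between modes, a C-section share q of 15% or 30%, and a within-mode SD s. The variance in an arm is then 24² q(1 − q) + s². For example, with q = 0.15, s = 6 h in intervention and 12 h in control, the variances are 73.44 + 36 = 109.44 and 73.44 + 144 = 217.44. The ratio is √(217.44/109.44) = 1.41 and the size is 7.9%. Across within-mode SDs of 6 to 12 h (intervention) and 9 to 18 h (control), with control the more variable, the ratio runs from 1.13 to 1.91 and the size from 6.0% to 10.5%. With equal within-mode SDs the size is 5.0%. With intervention the more variable (12 h against 9 h) it is 3.8% to 4.0%.

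**Counts.** For Poisson counts with equal rates the two arms have equal variances. At rates of 0.05, 0.1 and 0.3 the pooled test gave 4.9%, 5.2% and 5.0% in simulation.

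**The case against.** The strongest objection is that the protocol names a family of test, and that its exact form is normally settled in an SAP, which is not shown here. Section 4.3 never specifies equal variances. That much is true, and an SAP naming Welch would dispose of the point. But the section does choose a test by name, the ordinary meaning of that name is the pooled form, and nothing in the list points elsewhere. This is a stated method that can be improved, not a missing detail.

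A second objection is that the direction for length of stay is not known. This stands. No SD is given. Section 3.4 leaves discharge to the attending clinician and lets women stay longer without leaving the study. Section 3.2.2 delays randomization in both arms until suitability for early discharge is confirmed. All of this narrows any difference in spread. For BSES and EPDS, nothing in the protocol suggests that the arms would differ in spread at all.

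A third objection is that size at equal means is a poor measure for an outcome whose mean the intervention is meant to shift. This has some force. However, the standard error is misstated by the same factor k whether or not the means differ, so the strength of evidence would still be overstated or understated.

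A reader might go further and infer three things that the protocol does not support:
- *That visit and readmission counts are assigned to the t-test.* No test is assigned to any outcome, and as proportions they could go to chi-squared or Fisher's exact test.
- *That false positives are inflated for those counts.* With equal Poisson rates the pooled test keeps its level.
- *That planned confidence intervals are wrong.* Section 4.3 plans 95% intervals for the primary-outcome model only.

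**Conclusion.** The point holds in limited form. Student's t is the only listed test for secondary outcomes compared as means, and in its pooled form it is sensitive to unequal variances because the trial is 2:1. If control is the more variable arm, by an assumed SD ratio of 1.25 to 2, a nominal 5% becomes about 6.8% to 10.9%. If intervention is the more variable, the test is conservative (2.6% at a ratio of 0.67). If the spreads are equal, nothing is lost.

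The conclusion rests on reading Student's t as the pooled test and on SD ratios that the protocol does not supply. For length of stay the anti-conservative direction is plausible, not shown. The primary outcome is unaffected. This is a minor but nearly free improvement.

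**What to change.** In section 4.3, replace Student's t with one of the following for length of stay, BSES and EPDS:
- preferably, linear regression on arm with the stratification factors already used in randomization (site and parity) and heteroscedasticity-robust standard errors; or
- Welch's unequal-variance t-test, if an unadjusted comparison is wanted.

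The cost is a few lines of wording and routine programming. No new data are needed, and almost nothing is lost if the variances turn out equal.

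Two further changes are optional and do not follow from the variance calculation: a count model for emergency visits and readmissions, and a single repeated-measures model for BSES over its three time points.
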